# V. PROCEDURES

## Procedures timeline

### 1.1 Pre-TCE activities including community engagement

Potential villages will be visited and meetings organized with the local population and their leaders to explain the objectives of the project and to understand whether participation is acceptable and feasible. Community consent will be needed to proceed further. Five or more candidate villages, each with stable population sizes of about 250-1200 in each site will be selected based on criteria such as: easy access for community engagement and located where samples can reach the laboratories in less than 24 hours before processing. Once the study villages are chosen they will be visited regularly to engage with and prepare the community. A census will be performed and houses, work areas, and relevant migration routes will be GIS mapped. The final four villages per site will be chosen for TCE implementation based on a dry season malaria prevalence > 10%. Two of the four villages will be non-TCE control villages, two TCE. The control villages will be informed that they will receive TCE in the second year if the pilot TCE proves successful. After consultations and community engagement, health posts in each village will be set up. A presurvey where 1.5ml blood samples from 50 healthy adult volunteers in up to 20 villages will be conducted to establish sub-clinical pf malaria prevalence by qPCR.

**Community engagement**

A team of between 4 and 8 people depending on the size of the village and local resources, previously trained in community mobilisation activities, will be based at the village during 1-2 months preceding the first round of TCE and will remain in the village throughout the 12 months duration of the study. Specific community engagement activities will vary depending on the site’s population ethnicity and cultural and social background. The team will interact with the villagers at different levels to inform the community and engage it to participate in TCE implementation. Initial approval and support from the village leader with be sought. TCE purpose, procedures and expected risks and benefits will be explained as part of all community activities and meetings with villagers. These activities will include a diversity of events such as school sessions to engage children and their families, concerts, movies, plays and puppet shows performed on local holidays and written to convey information in an informal, entertaining way. Lunches and meals will be part of the events and will be designed to include teaching sessions. Focus group discussions (FGDs) will be conducted in groups of 8-12 representative individuals to discuss the purpose and benefits of TCE guided by community engagement trained staff. These activities will be all followed by Q&A sessions where specific questions can be raised by attending villagers of any age, which can then be used to modify the education activities according to the audience’s response. Quantitative and qualitative tools will be used to explore the understanding of the villagers of the project before and after the drug administration.

### 1.2 First exhaustive cross-sectional surveys and first TCE round

Exhaustive cross sectional surveys will be carried out in the selected villages (4 per site). Depending on the village size and level of participation, a total of about 3 days per village will be needed to conduct the first TCE round and associated survey. Individual informed consent will be asked from all participants or their attending relatives in individuals under 18 years of age (or lower depending on local guidelines). The samples (3 mL for participants 5.0 years and older, 0.5mls for those below 5 years) will be used for parasite DNA detection and gametocyte RNA assessment in those with >1000 copies/µL.

For each participant, in the TCE villages, blood sampling will be followed by a full treatment course of DP (total treatment of 3 days) plus PQ 0.25 mg/kg single dose. We will use the census data to follow-up and treat at home people who miss rounds of treatment; we will also follow-up at home any residents who miss cross-sectional surveys so that we can collect samples. When participants miss treatment or surveys due to being out of the village, messages will be left at home. Participants will be identified by biometrics (e.g. fingerprint or iris recognition), which will be linked to a unique identifier and barcode. Identification methods will be discussed per village. Possibilities include that individuals will receive a notebook (1 per family), a carton card or a bracelet with the barcode which can be used for later identification. All houses will be geo-localized by GPS.

### Second and third rounds of TCE and cross-sectional surveys

New rounds of 3 days treatment with DP+PQ will be administered to all participants of the 2 TCE villages at each site. Representative cross-sectional surveys will be carried out at monthly intervals.

-

### 1.4 Post-TCE survey

In all 4 study villages in each sites the exhaustive surveys will be repeated for detection of falciparum DNA and gametocytes as in the pre-TCE survey (see 2.1 below)

### 1.5 Follow up

Follow up period in all villages; all cases of clinical malaria in the residents as well as in the newcomers or visitors will be documented treated with a full course of DP. Throughout the study, the selected villages will be monitored closely. In both types of villages (TCE and non-TCE control) all inhabitants will be identified and given a unique ID number, and all houses will be geo-localized by GPS. The health posts’ activities will be closely supervised and malaria cases detected will be documented. Departures and arrivals of people will be documented. The community engagement teams will visit the villagers frequently and closely collaborate with the village leaders to strengthen participation. If a villager misses a TCE round or survey, then the study team will make attempts to follow up the person at home and by phone. If these attempts are not successful, a message will be left with the family head so that the team is informed when they return. People who leave the village for an extended time will be administered a catch up treatment or surveyed when they next become available. If newcomers arrive between surveys, they will be offered the option to become part of the study for as long as they are residents in an area where TCE is implemented, and also in the control villages newcomers will be identified, consented and surveyed.

### 1.6 Second year

In year 2 the control villages will receive TCE while the year 1 TCE villages will be observed. However this will be reviewed based on the results of the first year. A decision on the need to conduct TCE during a second year will be based on the prevalence measures at month 12 in the TCE villages. More sites in areas of known artemisinin resistance will be added in subsequent years should TCE prove successful in reducing malaria prevalence by ≥95% from baseline levels.

## Type and timing of surveys

There will be two types of surveys conducted throughout this study. There will be exhaustive cross-sectional surveys every 3 months on all village residents who consent to be surveyed (including those not enrolled initially for TCE), and the second type of survey will be on a smaller number of random samples once monthly.

### 2.1 Cross sectional surveys

Cross sectional surveys will be conducted on the entire village population who consent to be surveyed (including those not enrolled initially for TCE) starting with the first TCE round, then one month after the final round of TCE and thereafter at 3 month intervals. The approximate timing of the cross sectional surveys will be:

- First survey with TCE first round (month 0)
- First post-TCE (month 3)
- Post-TCE month 6
- Post-TCE month 9
- Post-TCE month 12 (1 year)

### 2.2 Other surveys

Additional surveys will be conducted on all *P.falciparum* carriers (or if the species cannot be determined) at monthly intervals to assess parasite and gametocyte dynamics. These surveys will be conducted from month 2 onwards throughout the first year.

### 2.3 Sample processing

At each survey, tympanic temperature will be measured and a very brief history of recent illness and travel will be obtained from each individual. Blood samples will be obtained consisting of 3.0 mL venous blood from all participants > 5.0 years and older, 0.5 mls for anyone below five. The samples will be used to detect asexual parasites (blood smear, sensitive PCR), parasite population structure (Sequenom genotyping and sequencing), gametocytes (microscopy, mRNA), Full blood counts (Sysmex where available) and hematocrits (or hemoglobin). The samples will be stored in a cool box in the field and then transported within 12 hours to the local laboratory for processing. Packed red blood cells, plasma and buffy coat will be separated, frozen and stored. The packed red cells will be transported frozen to the molecular laboratory at MORU for sample processing (DNA extraction or RNA isolation, quantitative PCRs). Plasma will be transported frozen to MORU for sample processing (a) immunological assays including antibody responses to malarial antigens and b) C-reactive protein levels). All samples for molecular analyses will be taken, handled and processed according to the SOPs developed specifically for these studies. If feasible, a 5 ml blood sample will be collected from all study participants who test positive for P.f. malaria during the study; this is for whole genome sequencing of the parasite. This may not be possible in some settings.

Suspected malaria patients will be tested on site by RDT and treated immediately if positive. Visitors and migrant cases will be documented.

## Drugs

The pilot TCE programme will be implemented via directly observed therapy (DOT) administration of an ACT treatment consisting of dihydroartemisinin-piperaquine (DP) accompanied by single dose primaquine (PQ) DOT will be administered at the health post.

One DP tablet contains 40 mg of dihydroartemisinin and 320 mg piperaquine. A weight-based regimen containing a total dose of approximately 7 mg/kg dihydroartemisinin and 55 mg/kg piperaquine phosphate will be used.

PQ 0.25 mg/kg single dose will be administered on day 1 of the 3 days DP regimen

## TCE protocol

All participants who have provided informed consent in the TCE villages will be given directly observed therapy (DOT) with DP for 3 days (target total dose of approximately 7 mg/kg dihydroartemisinin and 55 mg/kg piperaquine) plus low dose PQ (0.25 mg/kg, given on day 1 of DP). The drugs will be taken under supervision of the study team. These treatments are part of the National Treatment Guidelines in all countries where TCE will be implemented. The same procedure will be repeated monthly for 3 months. Thus, a total of 3 TCE treatments given in months 1, 2 and 3 will result in 3 rounds of TCE per year of study. Access to diagnosis and treatment will be similar for the paired TCE and non-TCE villages. A health post with RDTs and ACT+PQ for treatment will be established and regularly visited and re-supplied. Male and female villagers aged older than 6 months are the target study population and must meet the following inclusion and exclusion criteria.

### Inclusion criteria

- Age ≥6 months, male or female,
- Written informed consent (by parent/guardian in case of children)

### Exclusion criteria

- Pregnant women will not receive primaquine (urine pregnancy tests will be performed on women of appropriate age groups before drug administration at each TCE round)
- History of allergy or known contraindication to artemisinins, piperaquine or PQ
- Those who are, in the opinion of the study clinician, ill at the time of drug administration

### Withdrawal criteria

Each participant has the right to withdraw from the study at any time. In addition, the investigator may withdraw a participant if he/she considers it necessary for any reason including:

- Significant non-compliance with treatment regimen or study requirements
- Inablility to tolerate the medications i.e. and AE or SAE that necessitates withdrawal
- Loss to follow up

### Informed consent and eligibility

Participants will be screened by the study team to assess eligibility. Basic demographic and epidemiological data will be recorded by the study staff. Physical examination will be conducted by a qualified investigator. Weight and temperature will be recorded. All prescribed or over-the-counter and traditional medications used within the last 7 days will be recorded. Any drug allergies will be recorded. Screening tests will be performed as parasite counts from Giemsa or Field stained thick and thin blood films or malaria RDT, full blood count or haematocrit or Hb (depending on local resources) and urine pregnancy test for females of child bearing potential.

## Evaluation of participants’ perception, tolerability, safety and acceptability of TCE

The drugs used have been registered or evaluated extensively for malaria treatment but not as much as part of TCE. During the month 3 and the month 12 surveys a questionnaire will be administered to participants or their caregivers to evaluate perception, acceptability, tolerability and safety. Acceptability will be assessed both in terms of drugs received and possible side-effects as well as surveys requiring blood samples. Questions will specifically address whether individuals who refuse to participate or withdraw within the first three months because of unwillingness to give blood samples for the surveys would have joined the study (or not withdrawn) if it had involved receiving TCE without the need to give blood. Focus group discussions (FGDs) as well as in-depth interviews (IDIs) will be conducted to evaluate acceptability. IDIs will include the village leader as well as representative men, women and care givers per village. FGDs and IDIs will be moderated by trained staff based at the village.

The drugs used have been registered or evaluated extensively for malaria treatment but not as much as part of TCE. The months 3 and month 12 surveys questionnaires administered to participants or their caregivers will evaluate safety and will document adverse events (AEs). In this study, an AE is either a drug-related side effect or a new or exacerbation of a pre-existing symptom, sign or illness (other than malaria). A serious AE is one that results in death or is life-threatening, requires inpatient hospitalisation or prolongation of existing hospitalization. All SAEs must be reported by the site investigator to the Medical Monitor or his designee, within one day of his or her awareness of the SAE, who will then report to the study Data Safety Monitoring Board (DSMB). The site investigator must also report the SAEs to the local ethics committee in accordance with local requirements.

In a subsample of up to 10% of the study population a electrocardiogram will be obtained before and after the drug administration to document the safety of the study medication.

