## Secondary endpoints

Secondary endpoints will be:

- Safety and acceptability of TCE evaluated by questionnaires filled out by participants or care givers
- Effect on gametocyte carriage by TCE (measured by the proportions of gametocyte carriers over the 12 month period)
- The effect of TCE on the incidence of clinical malaria in the villages over the first 12 months
- Molecular analysis of parasite genotypes, markers of resistance and parasite population genetic structure
- Acceptability of TCE in the four study villages
- Cost estimates of TCE by sampling strategy

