# IV. STUDY DESIGN

## Type of study

This is a cluster randomized, controlled, not-blinded clinical trial including residents of four Lao villages. Two villages will receive the intervention (TCE) and the other two will be the controls. The control villages will help explain non-TCE related trends in malaria prevalence over the year such as seasonal effects as well as changes in detectable falciparum over the year in the absence of treatment and on the infectivity of non-clinical parasitaemia. Five or more villages will be pre-surveyed first leading to selection of four villages per site, of which two will be randomised to TCE and two to non-TCE control. The control villages will be TCE treated the following year should TCE prove successful.

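### The acceptability questionnaire has no stated route to most people who refuse or withdraw over blood sampling, although one of its questions is about them; separately, the four-village endpoint needs reconciling with two TCE villages

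*Protocol*

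**What the plan says.** Acceptability is part of the primary objective (Protocol section II) and appears twice among the secondary endpoints (section III.2): once with safety, measured by questionnaire, and once as "Acceptability of TCE in the four study villages".

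Section V.5 gives the method: "During the month 3 and the month 12 surveys a questionnaire will be administered to participants or their caregivers". It splits acceptability into two components, the drugs with their side effects and the surveys that require blood. It adds a specific question about "individuals who refuse to participate or withdraw within the first three months because of unwillingness to give blood samples": would they have joined, or stayed, if TCE had come without blood sampling? Focus groups and in-depth interviews are to supplement the questionnaire.

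The surveys that carry the questionnaire are "conducted on the entire village population who consent to be surveyed" (section V.2.1), and that section expressly includes people not enrolled for TCE at the start. At each survey, "Blood samples will be obtained consisting of 3.0 mL venous blood from all participants" aged five and over, with a smaller sample from younger children (section V.2.3).

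On the number of villages, section IV.1 states: "Two villages will receive the intervention (TCE) and the other two will be the controls".

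**The concern.** The question about blood sampling is useful only if it is put to people for whom blood sampling was the obstacle. As written, it is attached to visits at which blood is taken from people who have agreed to be surveyed. Someone who declined or left because of the needle is the resident least likely to be there.

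Two things are at stake. First, the protocol presents the pilot as a prelude to scale-up (section I) and wants coverage as close to complete as possible (section IV.2). Whether blood draws reduce uptake bears directly on both, since a later programme might not need them. Second, an acceptability figure taken from attenders leans towards those who accepted the procedures.

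A separate matter is scope. The endpoint names four villages, but two of them receive no TCE before the month 12 questionnaire, so acceptability of drugs received has nothing to measure there in year 1.

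**Working it through.** The protocol states no target, denominator or precision for acceptability, so there is no figure to reproduce. The check is mainly a comparison of sections.

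**Is there a route to those who refuse or withdraw over blood?**

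1. *Questionnaire (V.5).* It is given to participants or caregivers at months 3 and 12. Someone who refuses at month 0, or withdraws before month 3, has already left before it is first used.
2. *Survey population (V.2 and V.2.1).* It is the "entire village population who consent to be surveyed (including those not enrolled initially for TCE"). The bracket admits residents who declined the drugs but accept the survey. It does not provide for residents who decline the blood draw, which is part of each survey (V.2.3).
3. *Home follow-up (V.1.2 and V.1.5).* Section V.1.2 follows up residents who miss a survey in order to collect their samples, which is the step this group declined. Section V.1.5 adds home and telephone contact for missed rounds or surveys, leading to catch-up treatment or a survey. Neither mentions a questionnaire without blood.
4. *Withdrawal (V.4.3).* It gives the right to withdraw but no exit question.
5. *Focus groups and interviews (V.1.1 and V.5).* Interviews include the village leader and representative men, women and caregivers. The community-engagement focus groups have 8–12 representative people. Neither is confined to survey participants, so some refusers may be heard, but neither seeks them out. Neither can estimate what share of refusers would have joined without blood sampling.

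The protocol therefore states the intent to ask but no route that reaches most of this group.

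**Illustration of size, on assumed values.** Let a be acceptability among respondents, r the share of residents not reached, and b acceptability among those not reached. Acceptability over all residents is

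(1 − r) × a + r × b.

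Take a = 95% (assumed), with b from 0% to 50% (assumed):

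| r | b = 0% | b = 50% |
|---|---|---|
| 5% | 0.95 × 0.95 = 90.3% | 0.9025 + 0.025 = 92.8% |
| 10% | 0.90 × 0.95 = 85.5% | 0.855 + 0.05 = 90.5% |
| 20% | 0.80 × 0.95 = 76.0% | 0.76 + 0.10 = 86.0% |
| 30% | 0.70 × 0.95 = 66.5% | 0.665 + 0.15 = 81.5% |

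An attenders-only figure would read 95% in every row.

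**Four villages or two?** TCE goes to two of four villages in year 1 (IV.1). The control villages receive it only in year 2, subject to review of the first year's results (IV.1 and V.1.6), which is after the month 12 questionnaire. Of the two components in V.5, acceptability of drugs received can therefore be measured in 2 of 4 villages during the first 12 months, and acceptability of the blood surveys in all 4.

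**The case against.** The strongest reply is that the surveys fix when the questionnaire is given, not who may answer it. No section makes answering conditional on giving blood, and section V.5 states outright that refusers are to be addressed. Someone who declined at first may consent at month 3 or 12. Focus groups and interviews are open to non-participants, and section V.1.5 already sends staff to the homes of people who miss a round or survey. This stands against one reading that a reader might infer, namely that the surveys exclude refusers by definition. The documents do not support that. It does not supply the missing route: the stated respondents are participants or their caregivers, and the planned home contacts serve sampling, catch-up treatment or survey.

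On the villages, the objection is largely right. Blood-survey acceptability exists in all four. The endpoint naming four villages specifies neither instrument nor time point, and control villagers' willingness to receive TCE later is a fair question. Nothing says that the four villages will be pooled into one figure. What remains is an inconsistency of scope to be reconciled.

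On size, it is fair to say that scoring every refuser as finding TCE unacceptable would prejudge the very question being asked, since some may object only to the needle. That is why a range is shown.

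Finally, denominators and reporting sets commonly belong in a statistical analysis plan, which is not at hand. But whom the field team asks, and when, is a study procedure. An analysis plan cannot recover answers that were never collected.

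**Conclusion.** The point holds in limited form. Followed as written, the protocol leaves most people who refuse or withdraw over blood sampling without a stated way of being asked the question meant for them, and its acceptability results will lean towards attenders. The size is unknown because no refusal rate is given. Under the assumptions above, the gap from a 95% attenders' figure runs from about 2 to 5 percentage points with 5% not reached to about 14 to 29 points with 30%.

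A reader might infer that the acceptability endpoint as a whole misses its target. It does not: it reaches TCE recipients and survey attenders, and the gap concerns the refusal and withdrawal question. Nor does the village count support that inference. A scope that is too wide is a different problem from people being missed.

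This affects a secondary endpoint and one part of the primary objective. The primary endpoint (qPCR prevalence at 12 months) and the sample size are untouched. It is still worth correcting before the surveys begin, because reasons for refusal are hard to recover later.

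**What to change.** 1. In section V.5, add a short question set, separately consented and without blood, to be asked at the time of refusal or withdrawal, or at the home follow-up in sections V.1.2 and V.1.5. It should record the reason and whether the person would have joined or stayed without blood sampling.
2. Report acceptability alongside the number of eligible census residents who refused or withdrew, their reasons, and how many answered.
3. In section III.2, reconcile the four-village wording with the two TCE villages: report acceptability of the drugs received for the TCE villages, and acceptability of the blood surveys for all four. If control villagers' willingness to receive TCE is of interest, label it as such.

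The cost is a short form and a wording change for ethics approval. The census, the resident teams and the home visits are already planned. The downsides are that the acceptability result may be less favourable and that some refusers will decline these questions too, so non-response in this group should be shown.

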**Primary objective:**

To assess the feasibility, safety, acceptability, efficacy and effectiveness of TCE with DP + PQ as a tool for eliminating falciparum malaria

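### Non-serious adverse events are documented only by recall questionnaires at months 3 and 12, with no stated enquiry during or after each dosing round

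*Protocol*

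**What the plan says.** Section II gives the primary objective as "To assess the feasibility, safety, acceptability, efficacy and effectiveness of TCE with DP + PQ as a tool for eliminating falciparum malaria". Section III makes safety a secondary endpoint and names the instrument: "Safety and acceptability of TCE evaluated by questionnaires filled out by participants or care givers". Section V.5 fixes the timing: "The months 3 and month 12 surveys questionnaires administered to participants or their caregivers will evaluate safety and will document adverse events (AEs". It counts as an adverse event any drug side effect, and any new or worsened symptom, sign or illness other than malaria.

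Dosing is supervised by the study team over three days in each of three monthly rounds (V.4), and section V.3 places it: "DOT will be administered at the health post". The community engagement team "will remain in the village throughout the 12 months duration of the study" (V.1.1). Neither the dosing contacts nor the resident team is given the task of recording adverse events.

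Some safety information is collected outside the questionnaires. Serious events go to the Medical Monitor within a day of the site investigator learning of them, and from there to the DSMB. ECGs are taken before and after drug in at most 10% of the population (both V.5). Each survey includes a short illness history and blood counts or haematocrit (V.2.3).

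**The concern.** Section VII expects gastrointestinal symptoms, dizziness, headache and poor sleep, mostly below 10%, with dizziness near 12%. Such symptoms usually pass within days. A participant asked weeks or months later may have forgotten them, or may be unable to say which of three rounds they followed.

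This matters because section V.5 itself says that these drugs have been studied less in TCE than in treatment, and section I presents the pilot as the step before scale-up. Tolerability of repeated rounds in people who are mostly not ill is one of the things the trial should report. Incomplete recall pulls non-serious event rates down and can blur any change from round to round. Events not recorded near the time cannot be recovered later.

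**Working it through.** The protocol states no figure here that can be reproduced. The check is one of timing.

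**Inputs.** Enquiries at months 3 and 12 (V.5). Rounds at months 0, 1 and 2, because V.2.1 puts the first round at month 0 and the month 3 survey one month after the last round. Rounds in months 1, 2 and 3 according to V.4.

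**Lag = survey month − round month.**

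| Round timing | Month 3 questionnaire | Month 12 questionnaire |
|---|---|---|
| V.2.1: 0, 1, 2 | 3, 2, 1 months | 12, 11, 10 months |
| V.4: 1, 2, 3 | 2, 1, 0 months | 11, 10, 9 months |

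Under either timing, round 1 is first asked about at least 2 months later. Under V.4 the month 3 survey coincides with round 3. If the questionnaire came before that round's doses, the next enquiry about them would be 12 − 3 = 9 months later. The protocol does not say which comes first. The month 12 questionnaire looks back over 9 months since the previous one, a period without dosing under V.2.1, so it adds little on brief drug effects.

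**Do other data fill the gap?** Serious-event reporting covers serious events only. ECGs do not record symptoms and reach at most 10%. The illness history follows the survey calendar, and V.2.3 does not describe it as adverse event recording. Section V.4.3 allows withdrawal for an adverse event but does not say that the event is recorded or followed. For non-serious events, the questionnaires are therefore the only stated documentation.

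**Illustration only.** Observed rate = true rate × share recalled. The documents give no recall share. Assuming 30% to 90%:
- 12% dizziness: 12% × 0.30 = 3.6%, up to 12% × 0.90 = 10.8%.
- A 5% effect: 5% × 0.30 = 1.5%, up to 5% × 0.90 = 4.5%.

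The width of these ranges reflects the assumption. It shows direction and does not estimate the bias.

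**Records needed for the fix.** Per person: 2 DOT days × 3 rounds + 2 pre-dose checks (rounds 2 and 3) = 8. Per site: 2 TCE villages × 250 to 1200 people = 500 to 2400 people. At 8 records each, that is 4,000 to 19,200 records if everyone attends every round.

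**The case against.** The best defence is that the protocol makes a deliberate and openly stated choice. The primary endpoint is qPCR prevalence, and safety by questionnaire is a named secondary endpoint. The drugs are well known, and serious events have a separate, fast route. This limits the weight of the point, but it supplies no enquiry after a round.

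Several stronger readings are tempting, and the documents do not support them.

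- *Questionnaires are the only safety data.* Not so: serious-event reporting, ECGs, illness histories and blood counts are all planned. The word only holds for documenting non-serious events.
- *Events cannot be placed by round.* The questionnaire is not shown and could ask by round. Harder to attribute is as far as one can go.
- *Signals to the DSMB will be delayed.* The one DSMB route described is for serious events, and it starts from the investigator's awareness, not from the questionnaire.
- *Participants withdrawn for an adverse event will be missed.* Section V.4.3 lists intolerance and "Loss to follow up" as withdrawal reasons. However, surveys cover all consenting residents, including those not enrolled for TCE at the start, and absentees are followed up at home (V.1.2, V.1.5, V.2). Section V.5 also means to question some early withdrawers, namely those unwilling to give blood. Loss of these participants is a risk, not a stated consequence.
- *The definition of a serious event strengthens the case.* "A serious AE is one that results in death or is life-threatening, requires inpatient hospitalisation or prolongation of existing hospitalization" names no pregnancy outcome, while section V.4.2 says only that "Pregnant women will not receive primaquine". That is a separate matter from the timing of recall and carries no weight here.

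One further objection stands and shapes the fix. Checklists on DOT days exist only in TCE villages, so setting them against control-village survey answers would compare unequal ascertainment.

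**Conclusion.** The point holds in a limited form. For non-serious adverse events, the protocol states recall questionnaires at months 3 and 12 and no enquiry tied to a dosing round. The first enquiry comes about 3, 2 and 1 months after the rounds under V.2.1, or about 2, 1 and 0 months under V.4. Brief effects are likely to be under-counted and hard to attribute to a round.

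The conclusion assumes that the expected symptoms are mostly short-lived, since the protocol gives no durations. It also assumes that forgetting is not offset by over-reporting. A reader might take the illustrative percentages as an estimate of the bias, but its size is unknown. This is a weakness of method that can be improved cheaply; it does not touch the primary endpoint or leave serious events without a reporting route.

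**What to change.** In section V.5:

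1. Add a short adverse event checklist at contacts that already exist: DOT days 2 and 3 of each round, and before dosing at the next round. Let the month 3 survey close the last round.
2. State that participants who stop drug because of an adverse event stay in safety follow-up.
3. Report rates from DOT contacts descriptively, by round, for TCE villages only. Compare TCE with control villages only on questions asked identically in both at the surveys.

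Separately, reconcile the round timing in V.2.1 and V.4, and state whether the month 3 questionnaire comes before or after the last round's doses. The third-round lag, and the survey's use as the closing contact, depend on this.

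**Cost.** A one-page form, protocol wording, a few minutes per contact, and up to 8 short records per person, which is several thousand per site. No new visits are needed. Reported adverse event rates will be higher than with recall alone, and the report should say why.
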